## Abstract

**Aim:**

Non-alcoholic fatty liver disease (NAFLD) is currently the most prevalent liver disease in the world, increasing the risk of cirrhosis and hepatocellular carcinoma, and contributing to the development of type 2 diabetes, cardiovascular disease, and chronic kidney disease. This study aims to carry out a web-based continuum of a care intervention model to provide comprehensive care interventions for obese children with NAFLD, to improve the effectiveness of treatment of children with NAFLD.

**Design:**

A 1-year single-blinded randomized clinical trial in hospital in Zhejiang Province.

**Methods:**

Eighty subjects will implement the program in a randomized order. The interventions for the control group mainly consisted of the routine distribution of health education materials and health education by holding health-themed lectures, and the preliminary proposed interventions including establishing management teams, regularly delivering related health knowledge, daily uploading of health intervention records, regular supervision and mutual encouragement, home visiting and psychological guidance. The primary outcomes are serum biomarkers such as alanine aminotransferase (ALT) and gamma-glutamyl transferase (GGT), aspartate aminotransferase, and imaging (liver ultrasound and magnetic resonance imaging). Second outcomes are: BMI, waist-to-hip ratio and quality of life. In addition, socio-demographic characteristics such as age, gender and ethnicity will be recorded. Children aged 7–18 years old and diagnosed with NAFLD will be included, patients will be not eligible if they do not agree to participate or are participating in other health intervention programs. This study was registered on ClinicalTrials.gov (NCT05527938).

**Results:**

Over the past 30 years, NAFLD has been recognized as one of the most common liver diseases in adults and children. The current studies have focused on promoting lifestyle changes in children with NASH by providing some education and advice to children and their families to improve the histological features of NASH and lose weight. Because of the convenience and efficiency of the internet can provide some new strategies and ways for lifestyle interventions for children with NAFLD. In addition, we have designed a high-quality RCT based on the SPIRIT guidelines, which also provides strong evidence in this area.

## Introduction

With the development of economy and the improvement of material life, diet and living habits continue to change (excessive food intake, lack of exercise, etc.), over the past 30 years, the prevalence of overweightness and obesity among children and adolescents worldwide has increased at an alarming rate (1, 2). Nearly 1 out of every 6 children or adolescents in the U.S. has a body mass index (BMI) for age and sex above the 95th percentile and is considered obese (3).

Studies have found that the occurrence of fatty liver is directly related to the degree of obesity (4), and in recent years, non-alcoholic fatty liver disease (NAFLD) in children has surpassed hepatitis B as the most common liver disease in China (5). In children, the overall prevalence of NAFLD is 3–10%, rising to 40–70% in obese children (6). The prevalence of NAFLD in Asian and Chinese children is 6.3 and 3.4%, respectively (7). NAFLD is a clinicopathological syndrome of chronic hepatic steatosis involving more than 5% of hepatocytes in children and adolescents under the age of 18 years, excluding alcohol consumption and other definite causative factors leading to chronic fat deposition in the liver, and is a metabolic stress closely related to insulin resistance and genetic susceptibility The spectrum of disease includes non-alcoholic hepatic fat deposition. The disease spectrum includes non-alcoholic fatty liver (NAFL), non-alcoholic steatohepatitis (NASH) and its associated liver fibrosis and cirrhosis. Although fatty liver is a benign lesion and generally has little effect on children, it is often closely related to hyperlipidemia. It may develop into NASH and end-stage liver disease if not adequately diagnosed and treated, which may pose a potential threat to health and even life after adulthood, such as coronary heart disease, hypertension, and diabetes. It is a very important and urgent problem to reduce the incidence of childhood obesity and NAFLD.

Obesity is an independent risk factor for NAFLD, and the detection rate of fatty liver in obese children in China is 23.33% (5). Investigation shows that overnutrition and lack of moderate exercise are the main causes of obesity and fatty liver formation in children. Adjusting the diet and changing the lifestyle are the main interventions to control and prevent childhood obesity (8, 9), children have poor self-control and often fail to adhere to the planned measures, requiring the cooperation of parents, teachers, and doctors to supervise the implementation. Traditional interventions, in the process of implementation, are difficult to achieve the desired results due to time and frequency constraints, parental coddling, and lack of long-term effective and high-frequency participation and guidance from professionals, low compliance of the affected children.

Information technology has been increasingly used in the medical industry, from medical information records query to remote consultation and treatment, information technology has made a huge change in the traditional medical industry. The web-based continuity of care model based on new Internet technology can break traditional follow-up services' time and space limitations, expand service supply, improve service efficiency, and precisely match the diversified and multi-level health needs of nursing service recipients (10, 11). In this study, we followed the pace of the times. We tried for the first time the web-based continuity of care intervention model to provide comprehensive nursing interventions for obese children with NAFLD, always tracking their performance status, enabling them to grasp the knowledge of healthy weight loss, develop good lifestyle habits, and reduce their weight, thus reducing the incidence of NAFLD in children.

## Methods

### Reporting method

Following the Standard Protocol Items: Recommendations for Interventional Trails (SPIRIT 2013) checklist (12).

### Study design and setting

We will conduct a 1-year single-blinded randomized clinical trial. To recruit more study subjects, the study will conduct at a large hospital in Zhejiang Province (Figure 1).

**Figure 1 F1:**
[figure not shown]
Schematic diagram of the study design.

### Eligibility criteria for patients

In order to be eligible to participate in this study, patients should be: Children aged 7–18 years old and diagnosed with NAFLD: Referring to the Expert Consensus on the Diagnosis and Treatment of Non-Alcoholic Fatty Liver Disease in Children (13), the clinical diagnostic criteria need to meet 1–4 of the following, and any 1 of (5) or (6): (1) except for other pathological obesity; (2) in addition to the clinical manifestations of the primary disease, some patients may have non-specific symptoms and signs such as weakness, dyspepsia, vague pain in the liver area, hepatosplenomegaly, etc.; (3) overweight, obesity (centripetal obesity), elevated fasting glucose, lipid metabolism disorders, hypertension, and other metabolic syndromes; (4) alanine aminotransferase (ALT) is elevated more than 1.5 times the upper limit of normal value (60 U/L) and persists for more than 3 months; (5) liver imaging technique to diagnose hepatic steatosis; (6) histological changes in liver biopsy meet the pathological diagnostic criteria of fatty liver disease. Patients will not be eligible if they do not agree to participate or participate in other health intervention programs.

### Intervention

The interventions for the control group mainly consist of the routine distribution of health education materials and health education by holding health-themed lectures, and the preliminary proposed interventions are shown in Table 1.

**Table 1 T1:** Control group.

**Intervention**	**Intervention content and frequency**
Routine care	At each visit to the hospital, in this time, the child and his parents are given health education on diet and exercise booklets, and the parents supervise the child's daily life. The team members will review the child's condition every month for feedback.

To the above, the following four intervention components will be added, which shown in Table 2.

**Table 2 T2:** Intervention group.

**Intervention**	**Intervention content and frequency**
1. Establishing management teams	In addition to the subject leader, seven research team members will be each responsible for several participants (children with NAFLD) in need of intervention and formed a WeChat group for their parents.
2. Establishment of a nursing intervention team.	Composed of the Director of Nursing, a pediatric endocrinologist, a senior health lecturer and a nutritionist, three nurse leaders and a charge nurse with a master's degree. The director of the nursing department is the team leader. All members received half-month training from the team leader, including data collection, the purpose, model and implementation methods of the extended care intervention, and communication skills with the children and their parents. The training will be mainly in the form of intensive classes, and a theoretical examination will be conducted at the end of the training, requiring each member to pass.
3. Daily uploading of health intervention records	The nutritionist on the team develops personalized diet menu for each child based on age, height, weight, previous medical history, and any allergies, and at the same time, and an exercise therapist develops the tailored exercise plan for each NAFLD children (Appendix). The children and their parents upload the amount of exercise, and diet in the WeChat group every day, all parents can monitor and encourage each other in the group. Questionnaires are regularly posted in the group to judge the intervention effect and to adjust the implementation plan according to the individual intervention effect, with the aim of optimizing the plan and thus personalizing the intervention, and for subsequent studies we will consider using apps or WeChat applets for the intervention.
4. Regularly delivering related health knowledge.	Management team members Forming a WeChat group of children with NAFLD family members. Regularly through the WeChat platform, research team send relevant promotional materials such as nutrition knowledge and exercise knowledge to the children and parents 5 times per week, and we can also distribute some PPTs and videos of the professional nursing staff's promotional knowledge.
5. Home visiting	Members of the group made regular home visits, usually once every 2 weeks. The purpose of the visit is to grasp the development of the child's condition and to provide health education and dietary guidance to the child based on the visit results. If there is no one at home, it will be accessed by phone.
6. Psychological guidance.	The health teachers in the team should closely understand the psychological trends of the patients during the telephone follow-up and home visits and verbally communicate more with the children to stimulate them to develop good living habits and increase their confidence in healing.

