## Discussion

NAFLD is currently the most prevalent liver disease in the world, increasing the risk of cirrhosis and hepatocellular carcinoma, and contributing to the development of type 2 diabetes, cardiovascular disease, and chronic kidney disease (17, 18). BMI remains an important risk factor for NAFLD in children and young adults, and adipose tissue dysfunction contributes to the pathogenesis of NAFLD (19). General healthy eating advice and physical activity are recommended to promote weight loss in pediatric NAFLD. However, lifestyle interventions, be it general caloric restriction diets or low-fat or low-carbohydrate diets with or without increased physical activity, are frequently afflicted with low compliance and high drop-out and relapse rates in children and adults (20–22). In this study, we will implement the web-based intervention to provide more social and peer support to the affected child and family to improve their compliance with the intervention.

This current study has several strong features. Firstly, life-style interventions are the first step in managing children with NAFLD (14). The current studies have focused on promoting lifestyle changes in children with NASH by providing some education and advice to children and their families to improve the histological features of NASH and lose weight. As a previous systematic review mentioned, there is significant heterogeneity in study design quality, sample size, duration, outcome measures, and treatment interventions in RCTs for children with NAFLD. There is also a lack of effective and well-established lifestyle intervention programs to explore improvement in NAFLD. In addition, to our knowledge, web-based studies are currently being applied in adult NAFLD, providing web-based online training for those unable to attend face-to-face or group education (23). However, compared to adults, the child population is less sensitive to the Internet and adherent. Then, interventions for the entire population of children with NAFLD were not appropriately graded according to the severity of the disease, much less individualized for the different levels of intervention. Therefore, we used an adaptive strategy through Internet technology to implement individualized interventions according to each child's disease severity.

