There are also some limitations that need to be addressed. Firstly, we estimate that there will be an attrition rate of ~10% of children who enroll in the study, mostly due to financial issues or time constraints. To minimize the effect of the biases, we will conduct the analysis on an intention-to-treat basis. It is important to consider that although this study will be conducted in the hepatobiliary ward of a specialist women's and children's hospital in Shaoxing, Zhejiang Province, this may lead to limitations in the findings. However, we are conducting a formative evaluation throughout the implementation of the project to explore which interventions or environmental factors may hinder or contribute to the effectiveness of this project at different stages of implementation to facilitate global replication.

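### The trial is presented as evidence for web-based care, but the arms differ by a whole package including home visits and individual plans, so an effect cannot be credited to web delivery

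*Protocol article*

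**What the plan says.** **The label and the rationale.** The Abstract's aim reads "This study aims to carry out a web-based continuum of a care intervention model to provide comprehensive care interventions for obese children with NAFLD". The Introduction argues that a web-based model "can break traditional follow-up services' time and space limitations". The Abstract's Results paragraph points to the convenience and efficiency of the internet, and says the RCT will give strong evidence in this area. The Discussion states that "we will implement the web-based intervention to provide more social and peer support to the affected child and family" and attributes the individualisation of care to internet technology.

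**The intervention arm.** Table 2 (Methods, Intervention) is added on top of the control care. Its web elements are the parents' WeChat groups, daily uploads of diet and exercise, and health material sent through WeChat 5 times per week. It also lists:
- home visits: "Members of the group made regular home visits, usually once every 2 weeks", used to follow the child's condition and to give education and dietary guidance, with the fallback "If there is no one at home, it will be accessed by phone";
- a menu drawn up for each child by the nutritionist;
- an exercise plan drawn up for each child by an exercise therapist;
- psychological guidance during telephone follow-up and home visits.

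**The control arm.** Table 1 and the sentence above it list education booklets at hospital visits, health-themed lectures, parental supervision and a monthly review by the team. No home visits or individual plans are listed.

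**The design.** There are two arms of 40 (Sample size). Outcomes are measured to week 48 (Outcome).

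**The concern.** The reason given for the trial is that web delivery escapes the time and travel limits of conventional follow-up. Regular home visits are conventional follow-up, and they carry exactly those limits. Yet they sit in the intervention arm only, beside individual prescriptions that controls are not listed as receiving. If ALT or GGT improves more in the intervention arm, the WeChat support, the visits, the individual plans or the psychological guidance could each explain it.

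What is at stake is the conclusion. A reader who takes the trial as evidence for web-based care might reproduce the WeChat part and leave out the labour-intensive part, with no assurance from these data that the effect would survive.

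**Working it through.** **1. Components side by side.**

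| Component | Control | Intervention | Web-delivered? |
|---|---|---|---|
| Booklets, lectures, monthly review | yes | yes (Table 2 is added to this care) | no |
| WeChat group, daily uploads, messages 5 times per week | not listed | yes | yes |
| Home visits, usually every 2 weeks, phone fallback | not listed | yes | no |
| Individual menu and exercise plan | not listed | yes | written by professionals; route to the family not stated |
| Psychological guidance | not listed | yes | no (phone or home visit) |

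**2. Planned contact.** The article states no total number of visits, so there is no figure to reproduce. From the stated frequencies:
- Home visits per child to the last assessment: 48 weeks / 2 = 24. Over a full year: 52 / 2 = 26.
- Home visits for the arm to week 48: 24 × 40 = 960 at most.
- WeChat messages per family to week 48: 5 × 48 = 240.
- Home visits listed for controls: 0.
- Monthly reviews: about 12, or 11 to 12 depending on how the months are counted. Both arms receive them, so they do not offset the visits.

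The 24 is a ceiling, because the interval is qualified as usual rather than fixed and a missed visit becomes a call. The share of visits replaced by calls is not given. If it were a fraction f (an assumption), in-person visits would be 24 × (1 − f): 24 at f = 0 and 12 at f = 0.5. A phone call is not web delivery either, so all of this contact is outside the web component whatever f is.

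**3. What the contrast identifies.** Write the effects of the added elements as w (WeChat), v (visits or calls), p (individual plans) and g (psychological guidance), with i for any interactions. The randomised difference estimates

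Δ = w + v + p + g + i.

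This is one estimable quantity with several unknown terms. Every intervention child is allocated to all the elements and no control child to any, so no between-arm analysis separates w from the rest. Relating outcomes to contact counts within the intervention arm would not do it either, because the contact a family takes up is not randomised.

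**4. Definition of the package.** The text introducing Table 2 says four components are added, while the table numbers six. The package to which a conclusion would apply is therefore not stated consistently.

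**The case against.** The strongest reply is that the article describes a disclosed multicomponent package and never claims to isolate web delivery. Much of this stands:
- The aim goes on to speak of comprehensive care, and the Abstract's Methods openly lists home visiting and psychological guidance.
- No hypothesis about a single component is stated. A package against routine care is a legitimate design.
- Controls receive lectures as well as booklets and monthly reviews, so the contrast is not with booklets alone.
- The diet and exercise plans sit in the row on daily uploading, and Table 2 adjusts the implementation plan using questionnaires posted in the WeChat group. They are tied to the web platform even though professionals write them.

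A reader might also take the Discussion's plan "to explore which interventions or environmental factors may hinder or contribute to the effectiveness of this project" as a promise to identify effective components from the randomised comparison. The document does not support that. The sentence describes a formative evaluation run during implementation, which is a process evaluation separate from the randomised contrast. It can stand as such.

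What the reply does not remove is the mismatch. The model is named web-based in the aim and again in the Discussion, it is justified by the advantages of the internet, and the trial is offered as strong evidence in that area. The limitations do not mention that the effect cannot be attributed to web delivery.

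**Conclusion.** The point holds as one of attribution and labelling. The two-arm comparison can support a conclusion about the whole package against routine education. It cannot support one about web delivery, because web support is allocated together with up to 24 planned home visits per child to week 48 (calls where nobody is home), individual plans and psychological guidance.

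Two stronger readings are tempting but unsupported. One is that the comparison is biased: randomisation still gives an internally valid test of the package. The other is that each child will in fact receive 24 in-person visits: that figure is derived here, it is a maximum, and the number delivered is unknown. The data cannot say how much of any effect comes from the non-web elements. That is a limit on interpretation and does not show that web support is ineffective.

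The verdict assumes that controls receive only what Table 1 and its introductory sentence list, and that the visit frequency applies throughout the 48 weeks.

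**What to change.** - Restate the aim and planned conclusion as a multicomponent nursing package (WeChat support, home visits, individual diet and exercise plans, psychological guidance) compared with routine education.
- State in the limitations that no claim will be made for web delivery alone.
- Reconcile the count of four components in the text with the six rows of Table 2, so that the package is defined.
- Report the contacts actually delivered in the intervention arm: home visits, phone substitutes and uploads. Treat this as description.
- Keep the formative evaluation as a process evaluation, and say that its findings are not randomised evidence on single components.

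The cost is a few sentences and a tally of contacts the team is already making. Arms, care, outcomes, sample size and analysis do not change. The downside is a less attractive headline claim.

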### Outcome

The primary outcome are serum biomarkers such as alanine aminotransferase (ALT) and gamma-glutamyl transferase (GGT). Second outcomes are: aspartate aminotransferase, and liver imaging (liver ultrasound and magnetic resonance imaging), BMI, waist-to-hip ratio and quality of life. In addition, socio-demographic characteristics such as age, gender, and ethnicity will be recorded. All outcomes were measured at baseline, week 4, week 16, week 24, week 36, and week 48 to determine the trajectory of change in outcome variables over intervention process.

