### Assignment of intervention

Before randomization grouping, the children's medical records will be read carefully to obtain information about their demographics and diseases. Patients will be numbered according to the enrollment order and assigned to the experimental and control groups according to the random number table method. Statistical analyses will be performed to compare the balance of the two groups in terms of age, sex, ALT, BMI, and quality of life scores. The child's parents are entered into the same group as the child.

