### Data collection and management

First, members of the research team explained the purpose and significance of the study to the participants and obtained consent and support. Then, subjects who met the inclusion criteria were selected and the purpose, content, and significance of the survey were explained to them, explaining that the study results would be used only for scientific research and that medical confidentiality would be strictly observed. After that, the investigator personally distributed the questionnaire, and the patients filled it out under a uniform instructional language. For patients with no reading ability or writing difficulty but could understand and answer the questions correctly, the researcher will repeat the questions and options in a neutral tone, and the patients themselves chose. The researcher assisted in filling out the questionnaire, which will be distributed and collected on the spot. The questionnaires took about 25–30 min to fill out; finally, the researcher carefully check the collected questionnaires and promptly eliminated invalid ones. In addition, anthropometric measurements [length, weight, waist circumference (waist circumference) and blood pressure], blood sampling [serum alanine aminotransferase (ALT), insulin, glucose and lipids] and 1H-MRS were taken to determine hepatic steatosis. Use the collected height and weight data to calculate age-adjusted BMI-z scores (16).

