### Statistical analyses

First, after eliminating the questionnaires that did not meet the requirements, all data will be organized and quantified and then entered the statistical software in pairs for analysis. Then statistical description of the data will be done, including descriptive statistical analysis of patients' general information, the mean and standard deviation will be used to describe the measurement data that conformed to normal distribution. Finally, statistical inferences will be made and *t*-test, ANOVA. The effect of the intervention on NAFLD w analyzed using McNemar's test for paired categorical data and χ^2^ or Fisher's exact test for independent categorical data, as appropriate. Changes in continuous variables will be analyzed using paired Student *t*-test. Statistical significance will be set at *P* < 0.05. Using analysis of covariance we evaluated whether baseline variables predicted changes in liver fat content and ALT during 6 months of treatment.

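### BMI in growing children is a secondary outcome with no age adjustment stated and change is tested within group, while the BMI-z score already computed is used nowhere

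*Protocol article*

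**What the plan says.** All references are to the protocol article.

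- **Population.** Eligibility criteria for patients: "Children aged 7–18 years old and diagnosed with NAFLD".
- **Outcome.** The Outcome section, like the abstract, includes "BMI, waist-to-hip ratio and quality of life" among the secondary outcomes. BMI carries no qualifier for age, sex or scale.
- **Timing.** Outcome: "All outcomes were measured at baseline, week 4, week 16, week 24, week 36, and week 48".
- **Derived variable.** Data collection and management: "Use the collected height and weight data to calculate age-adjusted BMI-z scores". This is the only mention of BMI-z.
- **Balance check.** Assignment of intervention plans to "compare the balance of the two groups in terms of age, sex, ALT, BMI, and quality of life scores". It names BMI here, as does the list of baseline characteristics under Participant timeline.
- **Analysis of change.** Statistical analyses: "Changes in continuous variables will be analyzed using paired Student" t-test. The same section has "Finally, statistical inferences will be made and" followed by t-test and ANOVA, tied to no outcome or contrast. Its analysis of covariance asks whether baseline variables predict change in liver fat and ALT over 6 months; BMI is not among the responses.
- **Control.** Children are "assigned to the experimental and control groups according to the random number table method".

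**The concern.** Participants between 7 and 18 grow during a 48-week follow-up, so their BMI can move for reasons unrelated to adiposity or treatment, and at a pace that may differ by age and sex. The protocol seems to recognise this, since it derives an age-adjusted score. It then names plain BMI as the outcome and gives the score no role.

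The scale matters most because of the test attached to it. A paired t-test asks whether the mean within-child change in one arm differs from zero. For a growing child, zero change in BMI is not the same as no change in relative weight. The test therefore estimates growth plus treatment effect as one quantity.

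The interpretability of the BMI result is at stake. A null or unfavourable paired test in the intervention arm could mean that the programme failed, or that it worked and growth offset it. Leaving two scales in the document, with only one named as the outcome, also leaves room to choose between them after the data are seen.

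**Working it through.** **1. The plan's own figures.** The protocol gives no effect size, SD or growth rate for BMI, so there is no BMI figure to reproduce. From Sample size I use only the number of completers: 32 per arm, inflated for 20% loss as 32 / 0.8 = 40 per arm, 80 in total. That size was set for ALT; whether it is right for ALT does not bear on this point.

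**2. What each analysis estimates.** Let g be the mean age-related change in BMI over 48 weeks and e the mean effect of the intervention.

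- Paired test, intervention arm: expected change = g + e.
- Paired test, control arm: expected change = g, taking no effect in controls.
- Between-arm difference: (g + e) − g = e.

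The paired test is off by g. The between-arm contrast is not. If g varies with age and sex, the variance of an individual raw change is the residual variance plus Var(g), so the between-arm comparison on raw BMI loses precision but stays unbiased.

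**3. Size under the paired test (illustration).** The documents supply neither g nor the SD of change s. I assume g = 0.3 to 0.9 kg/m² and s = 1.0 to 2.0 kg/m². With n = 32, two-sided α = 0.05 and 31 degrees of freedom, rejection probabilities come from the non-central t distribution with non-centrality (g + e) / s × √32.

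*Growth alone (e = 0): probability of a significant BMI rise.* Example: g = 0.6, s = 1.5 gives 0.6 / 1.5 × 5.657 = 2.26, and 59.2%.

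| g | s = 1.0 | s = 1.5 | s = 2.0 |
|---|---|---|---|
| 0.3 | 37.6% | 19.4% | 12.8% |
| 0.6 | 90.8% | 59.2% | 37.6% |
| 0.9 | 99.9% | 90.8% | 69.4% |

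A false significant fall has probability at most 0.27% (g = 0.3, s = 2.0). A between-arm test with the same drift in both arms rejects in 5%.

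*True benefit (s = 1.5): probability of a significant fall in the intervention arm.* Example: e = −1.0, g = 0.6 gives −0.4 / 1.5 × 5.657 = −1.51, and 30.9%. Without growth it is −1.0 / 1.5 × 5.657 = −3.77, and 95.5%.

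| e | no growth | g = 0.3 | g = 0.6 | g = 0.9 |
|---|---|---|---|---|
| −0.3 | 19.4% | 2.5% | 0.1% | <0.1% |
| −0.6 | 59.2% | 19.4% | 2.5% | 0.1% |
| −1.0 | 95.5% | 72.5% | 30.9% | 5.5% |

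**4. Where the score goes.** BMI-z is absent from the abstract's outcome list, Outcome, Participant timeline, Assignment of intervention and Statistical analyses. It is calculated and then not used anywhere in the document.

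**The case against.** The strongest reply is that Outcome names the construct and Data collection and management gives its scale, so that BMI simply means BMI-z. The protocol never says that kg/m² will be analysed; that is an inference from the unqualified word. On this reading the growth artefact largely disappears. The objection stands as a caution, but it does not settle the matter: plain BMI recurs in the outcome lists, the baseline list and the balance check, nothing links the score to any of them, and the same edit removes the doubt.

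Second, the trial is randomised with a concurrent control, and the unattached t-test and ANOVA could be between-arm comparisons. This also stands. If they are, growth cancels in expectation. However, the one sentence that addresses change prescribes the paired test.

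Third, the paired test affects every continuous outcome, and an article may leave the analysis scale of a secondary outcome to a fuller document. True, but this article does fix a test for change, and for BMI that test combines with growth to give a result that cannot be interpreted.

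Three stronger readings are tempting and not supported:

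- *Growth would be mistaken for treatment response.* Response here is a fall in BMI. If BMI rises with age, growth works against a fall and masks benefit.
- *The randomised comparison itself is biased.* It is not; unadjusted BMI only makes it noisier. With ages spread evenly over 7–18 (assumed), the SD is 11 / √12 = 3.18 years, and the chance difference in mean age between arms of 40 has a standard error of 3.18 × √(2/40) = 0.71 years. That is random imbalance, not bias, and the documents give nothing with which to convert it to BMI units.
- *The percentages above are properties of this trial.* They follow from assumed inputs, and their width shows how far those inputs decide the answer.

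**Conclusion.** The point holds as a free improvement. The protocol names BMI without age adjustment as a secondary outcome in children aged 7–18, computes a BMI-z score that it never uses, and prescribes a within-group paired test that confounds age-related change with treatment effect.

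The confounding follows from the design of the test and needs no assumption beyond BMI changing with age. Its direction and size do rest on assumptions. With upward drift of 0.3–0.9 kg/m² and an SD of change of 1.0–2.0, growth alone makes the paired test show a significant rise in about 13% to more than 99% of trials. At SD 1.5, the chance of detecting a true fall of 1.0 kg/m² drops from 95.5% to between 72.5% and 5.5%. If BMI fell with age the direction would reverse.

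The consequence is limited to one secondary outcome and to the paired analysis.

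**What to change.** 1. In the abstract and in Outcome, replace BMI with the age- and sex-adjusted BMI-z score described under Data collection and management, and state that BMI in kg/m² is reported descriptively only. That section mentions age adjustment alone, so add sex there too.
2. In Statistical analyses, replace the paired t-test for this outcome with a between-arm comparison at week 48 adjusted for baseline: BMI-z at week 48 = intercept + arm + baseline BMI-z, reporting the adjusted arm difference with its 95% confidence interval.

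For consistency, Participant timeline and Assignment of intervention could name BMI-z as well, but the point does not depend on it.

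**Cost.** Wording only. Height, weight, age and sex are already collected and the score is already calculated. There is no extra visit, measurement or participant. The change should be dated before anyone sees outcome data by arm.
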